### Trial design {8}

We will conduct a stepped-wedge, randomized clinical trial of a multi-faceted educational and care-process based intervention designed to improve the guideline-concordant care of patients with BPPV in the emergency department. The overall design includes an ED-level implementation and embedded, patient-level dissemination strategies which will allow evaluation of both implementation and effectiveness outcomes. Our study design and proposed methods are aligned with methodological standards in a stepped wedge, randomized clinical trial. The overall study period will be approximately 24 months. The study will start with a 6-month pre-intervention period. This will be followed by staggered intervention at the 15 EDs in 11 waves (some medical centers will be paired based on the medical service area) and then an approximately 6-month post-intervention period. The order that each ED receives the intervention will be randomized. The intervention will be provided as a complete package during the month each hospital is randomized. Concurrently, patients will be recruited before and after the physician level intervention is implemented at each ED. Enrolled participants will complete a survey to obtain baseline information and then randomized individually, stratified by sex, age, and medical center, to the intervention or control arm using central computerized randomization. The intervention arm will be sent intervention materials via patient specified preferred electronic communication. The control arm will be provided with the hospital’s standard post-discharge materials.

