## Data collection and management

### Plans for assessment and collection of outcomes {18a}

Enrolled participants will complete the dizziness handicap inventory survey to obtain baseline dizziness disability. Participants will be asked to complete weekly surveys for 4 weeks to measure dizziness handicap over time. The close follow-up will protect against loss to follow up. Computerized surveys will be used at follow up to assess patient reported outcomes. Generally, the participants will complete on their own on a computer or smartphone. The participants baseline survey includes the following elements.Dizziness characteristics: Including questions about the type of dizziness, duration, severity, triggers, and associated symptoms.Dizziness handicap inventory: Identifies dizziness disability and includes functional, emotional, and physical elements.Days out of role: self-report measure used by the World Health Organization to quantify the number of days a person was totally unable to carry out usual activities because of a health conditionPatient Health Questionnaire (PHQ)−4Patients will also be asked if a DHT or CRM was performed at or since the ED visit, when it was performed, and who performed it (self, provider, other)

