## Statistical methods

### Statistical methods for primary and secondary outcomes {20a}

The primary outcome is the dizziness handicap inventory (DHI) which is a continuous (0–100) measure of dizziness disability based on a patient’s responses to 25 survey questions. Higher scores indicate more disability. We will use the Ceballo validated Spanish translation for the Spanish speaking individuals. As a sensitivity analysis, we will substitute 2 Lopez questions because we did not think the Ceballo translation was optimal for the following questions: Does bending over increase your problem? (Ceballo: When you get up, does your problem increase?]-Does turning over in bed increase your problem? (When you get out of bed, does your problem increase?] The DHI outcome will be obtained at 1-week intervals after the ED visit for 4 consecutive weeks—corresponding to 4 assessments. We will obtain 4 weekly assessments as we expect that time to recovery will vary given our heterogenous dizziness population. The primary analysis will be a multi-level model as follows: dependent variable (outcome) is the DHI (continuous); fixed independent variables are ED-level intervention group (0/1), patient intervention group (0/1), an interaction term of ED-level intervention with patient intervention group, patient severity at the time of ED visit (continuous), and assessment number (categorical, 1–4); and including a random ED-level intercept. This method allows us to capture variability in recovery over time while maintaining all of the variation in our continuous outcome. We include the severity at the time of the ED visit measure in the model to adjust for baseline disability, protecting against any random imbalances. Because of the two concurrent interventions (ED-level [0/1], patient-level [0/1]), patients will be in either a no intervention group, an ED-level intervention group only, a patient-level intervention group only, or both an ED- and patient-level intervention group. For a secondary analysis, we will add an interaction term of assessment number and intervention group (i.e., a 3-way interaction term of ED-level intervention, patient-level intervention, and assessment number) to further evaluate if any association of intervention group with the DHI outcome is modified by time to assessment. We will make comparisons of the effectiveness of the intervention at each time interval by estimating average marginal effects from our secondary model and comparing marginal effects using Wald Tests. We do not anticipate that our interventions will have differential effects by sex, either at the patient or provider level. Dizziness presentations in the emergency department are more common in females, although at this point there is little biological understanding of the reason for this. For the patient level analyses, we will disaggregate the data and perform analyses separate for male and female patients to assess for heterogeneity. In secondary analyses, we will explore if patient factors (age, sex, Charlson co-morbidities, health literacy) modify the effect of interventions with the outcome. Health literacy will be measured at the first outcome assessment using the BRIEF health literacy tool, 80 which was selected using the Boston University Health Literacy Tool Shed.

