### Methods in analysis to handle protocol non-adherence and any statistical methods to handle missing data {20c}

Many participants will not complete all 4 surveys; however, the longitudinal models planned for the primary analyses above should account for this. When appropriate, multiple imputation will be used. Exploratory analyses may focus on how many physicians at a site used the CME intervention and if possible, we will conduct analyses evaluating the primary outcome within the subset of physicians who viewed the CME.

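### Health literacy, a planned effect modifier, is measured after patient-level randomisation and only in those who answer a follow-up survey

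*Protocol article*

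**What the plan says.** Section {20a} of the protocol article names four candidate modifiers: "In secondary analyses, we will explore if patient factors (age, sex, Charlson co-morbidities, health literacy) modify the effect of interventions with the outcome". For one of them it fixes the time of measurement: "Health literacy will be measured at the first outcome assessment using the BRIEF health literacy tool".

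The same section defines the outcome assessments: "The DHI outcome will be obtained at 1-week intervals after the ED visit for 4 consecutive weeks". They enter the primary model as "assessment number (categorical, 1–4").

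The baseline survey is a separate, earlier step. Trial design {8} gives the order: "Enrolled participants will complete a survey to obtain baseline information and then randomized individually, stratified by sex, age, and medical center". Section {18a} introduces the content of that survey with "The participants baseline survey includes the following elements" and lists dizziness characteristics, the DHI, days out of role, the PHQ-4 and whether a DHT or CRM was performed. Health literacy is not on the list.

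On response, section {20c} expects that "Many participants will not complete all 4 surveys". It relies on the longitudinal model and allows multiple imputation where appropriate.

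**The concern.** A subgroup comparison keeps the protection of randomisation when subgroup membership is settled before allocation and known for everyone allocated. Here neither condition is met for health literacy. Whether a participant has a value depends on answering a follow-up survey, which is mostly self-completed on a computer or smartphone. People with low health literacy may well answer less often, and response may also differ by arm. The low-literacy group could then be a selected one, and selected differently in the two arms.

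A second, weaker route is that the answers themselves shift. The patient-level intervention is health-education material, and the tool is completed after each arm has been allocated its own website.

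What is at stake is one exploratory interaction, but a relevant one. The background section on patient materials reports that patients often find online BPPV instructions confusing, and the sample size section appeals to the scalability of the interventions. Whether web-based self-care also helps patients with low health literacy is a question readers will bring to this trial.

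**Working it through.** The plan gives no figure to reproduce. The check is one of sequence, followed by an illustration of size.

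**Sequence for the patient-level intervention**

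1. Baseline survey, without health literacy ({8}, {18a}).
2. Individual randomisation ({8}).
3. Website link sent, a different one for each arm ({8}, {17a}). The interval between randomisation and sending is not stated.
4. Outcome assessments 1 to 4, weekly after the ED visit, with the BRIEF tool at the first ({20a}).

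Could the first outcome assessment be the baseline survey? The text does not allow it. Section {20a} counts four weekly assessments after the visit and numbers them 1–4, and it adjusts separately for severity at the time of the ED visit. Section {18a} describes the baseline survey and the weekly surveys as different things. Nothing in the article places the BRIEF tool at baseline or names a later collection point for those who miss the first assessment.

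**How the four modifiers compare.** Age, sex and Charlson co-morbidities do not depend on answering a follow-up survey. Health literacy alone does.

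**Size (illustration only)**

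Inputs: N of about 1,500, the likely final sample size in the revised sample size section; week-1 non-response *d* of 10% to 30%, which is an assumption because the article gives no rate.

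- Participants without the modifier = N × d: 1,500 × 0.10 = 150; 1,500 × 0.30 = 450.
- Standard error of a complete-case interaction relative to full capture = 1/√(1 − d): 1/√0.90 = 1.05; 1/√0.70 = 1.20.

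The second line assumes that responders and non-responders have the same spread of literacy and the same residual variance. It describes lost precision, not bias. Both lines are upper limits on what the placement of the tool costs: a participant who misses week 1 and never responds has no follow-up DHI either, so only those who answer a later survey are lost because of the missing BRIEF score.

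If *first outcome assessment* means the first survey a participant actually completes, only those who never respond lack a value. The missingness is then that of the outcome itself, but the measurement still follows randomisation.

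**The case against.** The case for leaving this alone has several sound parts.

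- The analysis is secondary and exploratory. Health literacy is not in the primary model, and full subgroup plans are deferred to the analysis plan. This stands and limits the weight of the point. A later analysis plan cannot, however, change when the data were collected.
- A reader might infer that the websites change BRIEF scores by arm and so create or hide an interaction. The documents do not support that. They do not describe the tool's items, both arms receive a website, and the time from randomisation to the first assessment is unstated and may be short. General health literacy is also fairly stable over a week. The shift is a possibility, not a demonstrated problem.
- A reader might infer that several hundred participants will be lost. The expectation of incomplete surveys in {20c} gives no week-1 rate and would also fit drop-out concentrated later. Multiple imputation is allowed. That objection stands against any firm number. Imputation reduces the loss but relies on missingness being explained by observed data, which is doubtful if low literacy itself drives non-response.
- The analysis concerns both interventions, and exposure to the ED-level intervention precedes enrolment. Even a baseline measurement would follow it. This stands: the point concerns the patient-level intervention only.
- Enrolment ended in March 2025 (Trial status), so the timing can no longer be changed for this cohort. This also stands and shapes the fix.

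**Conclusion.** The point holds in limited form. For the patient-level intervention, a named effect modifier is measured after randomisation and depends on follow-up response, although a survey before randomisation was available to carry it. The timing follows directly from the text. The consequences are less certain: selective missingness is the main concern and is plausible but undocumented, while arm-driven change in scores is probably small.

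Under the assumed 10–30% non-response and about 1,500 enrolled, 150–450 participants would lack the modifier, with a complete-case standard error at most about 1.05–1.20 times that under full capture. The document supports no narrower range. The primary DHI result and the other three modifiers are not affected.

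**What to change.** **Design.** Place the BRIEF tool in the baseline survey, before randomisation. The cost is a slightly longer baseline survey. The gain is a modifier known for essentially everyone randomised, and a means of checking whether later non-response depends on literacy.

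**For participants already enrolled:**

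- State whether *first outcome assessment* means week 1 or the first survey completed.
- Report BRIEF scores and BRIEF missingness by arm. Do not use a non-significant difference between arms as a licence to proceed; it does not show that the score is unaffected by allocation.
- Add a sensitivity analysis that includes participants lacking BRIEF through multiple imputation.
- Label the literacy interaction as exploratory and based on a post-randomisation measure.

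This costs one table, one sensitivity analysis and a sentence of labelling. A substitute from the medical record is not proposed, because the article documents no literacy measure or proxy there.

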### Sample size {14}

#### ED level

The Kaiser Permanente Southern California study site is comprised of 14 ED facilities, which collectively had nearly 40,000 dizziness visits in 2017. We plan to collect data on these visits for approximately 24 months. Thus, for the ED-level strategy, we will evaluate documentation of the DHT and CRM in >80,000 dizziness visits anticipating an increase in volumes over time. We hypothesize that the proportion of target visits with DHT/CRM documentation will increase from 7% in the pre-intervention period to 17% in the post-intervention period based on the findings in our estimated target population in DIZZTINCT-1. Even small absolute increases in the frequency of use of the DHT/CRM in the target population are considered clinically meaningful because the DHT and CRM are simple from a resource standpoint, not expensive, low risk and highly effective in clinical trials. With a sample of 80,000 visits, our power to detect an increase in DHT/CRM use from 7% in the control visits vs 17% in the intervention visits will be effectively 100% based on a two-sided test for independent proportions considering clustering at 14 sites, an intraclass correlation coefficient (ICC) by provider of 22% for provider-level variability (from DIZZTINCT-1) and a significance level of 5% (Table 1). We will use a mixed effects model to account for secular trends, hospital- and provider-specific features, and the potential relative association of the various components with the outcome. We estimate that 20% of the annual sample is the target population (80,000 × 0.20 = 16,000 visits) based on best available evidence that showed about 20% of dizziness patients in a national sample have BPPV characteristics. Of the 16,000 visits, approximately 8000 will be pre-intervention visits and 8000 post-intervention visits. With these volumes, we expect 560 (8000 × 7%) visits with DHT/CRM documentation in the pre-intervention period and 1360 (8000 × 17%) in the post-intervention period. Thus, we anticipate at least 1900 visits with DHT/CRM documentation. For modeling purposes, we should be able to easily meet and exceed the general rule of having 10 outcomes for each independent variable to avoid over-fitting. The large number of visits and anticipated outcomes will allow us to more closely examine differences at hospitals and provider types, and the relative influence of the various intervention components. We will be able to monitor use of the CME session, website, app, and reminder system and incorporate these variables in the model specific to the provider. The additional power will allow us to examine differences at hospitals and provider types, and the relative influence of the various ED-level implementation strategies.

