
We initially considered performing the analysis using time to event (Cox proportional hazard model) based on a fixed and pre specified percentage improvement in the DHI from baseline. We felt, however, that this approach had two important limitations. First, there is not an established DHI threshold of success to use for time to event, and the appropriate threshold likely varies by condition. Second, a time to event analysis would dichotomize a continuous variable which substantially comprises statistical efficiency, information, and precision (e.g., true difference in degree of DHI improvement), and power [12, 36, 47, 49].

SPIRIT guidance: Statistical methods for analyzing primary and secondary outcomes. The statistical analysis for secondary and exploratory outcomes will be multi-level regression models as with our primary outcomes. For the cost analysis, the inputs will include tests, medications, procedures, consultations, and level of visit. Additional costs will also be gathered relating to hospital admission and subsequent visits to the ED. Unit costs will be derived from nationally representative sources (e.g., Medicare fee schedule). Costs often have a skewed distribution and thus will be log-transformed to achieve a more normal distribution. The costs in patients treated by pre-intervention providers will be compared to costs in patients treated by post-intervention providers using the t-test and also a generalized linear model (GLM). General concepts for modeling costs will be followed. [40, 46] Reference to where other details of the statistical analysis plan can be found, if not in the protocol.

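### The planned pre/post t-test on costs is confounded with calendar time, ignores clustering and probably tests geometric means; the cost inference should rest on a time- and cluster-adjusted model of mean cost.

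*Protocol article*

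**What the plan says.** The cost methods are in the protocol article, Statistical methods for primary and secondary outcomes {20a}. Unit costs come from national sources: "Unit costs will be derived from nationally representative sources (e.g., Medicare fee schedule". On scale the text says "Costs often have a skewed distribution and thus will be log-transformed to achieve a more normal distribution". It then fixes the comparison: "The costs in patients treated by pre-intervention providers will be compared to costs in patients treated by post-intervention providers using the t-test". The same sentence names a second method, "using the t-test and also a generalized linear model (GLM", whose family, link, covariates, time term and cluster term are not given.

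Two other statements bear on this. Earlier in {20a} there is a general rule: "The statistical analysis for secondary and exploratory outcomes will be multi-level regression models as with our primary outcomes". In Sample size {14}, ED level, the text on Dix-Hallpike/canalith repositioning (DHT/CRM) use says "We will use a mixed effects model to account for secular trends, hospital- and provider-specific features".

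Trial design {8} describes 6 months before any intervention, 15 EDs switching in 11 waves, then about 6 months after the last switch: "The overall study period will be approximately 24 months".

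**The concern.** Every ED contributes pre visits early and post visits late. An unadjusted pre/post contrast therefore mixes the intervention effect with whatever else changed over that time: imaging habits, admission thresholds, staffing, case mix. A two-sample t-test has no place for a calendar term. It also treats visits as independent, although the protocol itself reports clustering for other outcomes (provider ICC 22% for DHT/CRM in Sample size {14}, ED level; ED-facility ICC 1.9% under Patient level). Neither is a cost ICC, but both show that independence is not the protocol's own view of these data.

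The scale is a separate matter. The log transformation is stated just before the t-test is named, so the natural reading is a test on log cost. That tests a ratio of geometric means, whereas a health system pays the arithmetic mean.

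The cost result has some weight: Sample size {14}, Patient level, argues that if care becomes more efficient, even a very small clinical gain would justify wide use. A spurious saving or increase could feed that argument.

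**Working it through.** **What can be reproduced.** The protocol gives no cost figure. The only related figure is the split of the 16,000 target visits into about 8000 pre and 8000 post. With equal ED volumes over 24 months and waves spread over the middle 12 months, the split is 50/50, which agrees. With strictly monthly waves from month 7 it is 46/54.

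**Calendar gap.** An ED that switches at month s of T gives s pre-months with mean date s/2 and T − s post-months with mean date (s + T)/2. Pooled:

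- pre mean = Σ(s²/2) / Σs
- post mean = Σ((T² − s²)/2) / Σ(T − s)

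For s = 6, …, 16 and T = 24: Σs = 121, Σs² = 1441, Σ(T − s) = 143. Pre mean = 720.5/121 = 5.95 months; post mean = 2447.5/143 = 17.12 months; gap = 11.16 months. With T = 23 the gap is 10.63; with waves spread over 12 months it is 11.01.

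**Spurious difference from trend (assumed rates).** With annual trend r and gap g, the log-cost shift is d = ln(1 + r) × g/12. At g = 11.01 and r = 1%, 3%, 5%, d = 0.0091, 0.0271, 0.0448, that is, geometric cost ratios of about 1.009, 1.028 and 1.046 with no intervention effect.

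**Rejection by the t-test with no intervention effect.** Assume log-cost SD σ = 1.0 and no clustering. SE = σ√(4/N), z = d/SE, rejection = Φ(z − 1.96) + Φ(−z − 1.96). For example, at N = 80,000 and r = 3%: SE = 0.00707, z = 0.0271/0.00707 = 3.83, rejection 97%. A simulation of 15 EDs in 11 waves gives the second figure in each cell.

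| N | 1% a year | 3% a year | 5% a year |
|---|---|---|---|
| 80,000 | 25% / 25% | 97% / 97% | 100% / 100% |
| 16,000 | 9% / 8% | 40% / 40% | 81% / 82% |
| 1500 | 5% / 6% | 8% / 10% | 14% / 11% |

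The differences in the last row are of the size expected from simulation noise (1000 replicates). The sizes are the protocol's visit total, its target-visit subset and the likely enrolled cohort; which of these the cost analysis uses is not stated. At 3% a year, a 12-month gap and σ from 1.2 down to 0.8, rejection is 94% to 99.9%, 34% to 65% and 7% to 11% respectively.

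**Clustering alone (no trend, ED ICC assumed 1.9%).** For 15 EDs with mean switch month 11, Σs = 165 and Σ(24 − s) = 195. An ED's weight in the post mean minus its weight in the pre mean is (11 − s)(1/195 + 1/165) = (11 − s) × 0.01119. The variance of months 6 to 16 is 10, so the squared weights sum to 15 × 10 × 0.01119² = 0.01878, and the extra variance is 0.019 × 0.01878 = 0.000357.

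- N = 80,000: naive variance 4/80,000 = 0.00005; true/naive = (0.000357 + 0.981 × 0.00005)/0.00005 = 8.1; SE ratio 2.85; type I error 2Φ(−1.96/2.85) = 49%.
- N = 16,000: ratio 2.41, SE ratio 1.55, type I error 21%.
- N = 1500: ratio 1.11, SE ratio 1.06, type I error 6%.

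The simulation gave about 51%, 22% and 5.5%. Trend and clustering do not simply add: at 80,000 visits and 3% a year, simulated rejection was 97% without clustering and 76% with it.

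**After adjustment.** Regressing log cost on intervention, linear month and ED fixed effects gave a mean effect within ±0.005 of zero in every scenario and rejection of 3% to 8%. This used a truly linear trend and no ED-by-period variation, so it shows that the bias is removable, not that this exact model suffices.

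**Scale.** For lognormal costs the mean is exp(μ + σ²/2). With equal geometric means and σ = 1.0 against 0.9 or 1.1, the mean-cost ratio is exp((0.81 − 1)/2) = 0.909 or exp((1.21 − 1)/2) = 1.111: differences of −9% or +11% that a test on log cost is not aimed at.

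**The case against.** The strongest reply is that the t-test is not the whole cost analysis. The GLM named beside it can model mean cost and carry period, ED and provider terms. Its details may properly sit in an analysis plan not shown here, and the article says general principles of cost modelling will be followed. This stands: a reader might infer that the entire cost analysis ignores time and clustering, and the documents do not show that. It does not rescue the t-test, which no further specification can adjust and which is listed as a comparison in its own right, with no priority stated between the two methods.

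A second reply is that the protocol already handles trend and clustering elsewhere. The sentence "We will use a mixed effects model to account for secular trends" belongs to the DHT/CRM outcome. The general rule on multi-level models refers back to the primary-outcome model; the DHI model in {20a} has a random ED intercept but no calendar term, so carrying it over would not remove a trend. Costs are in any case given their own methods. The sentences do suggest that the investigators are aware of secular trend.

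Third, the false-positive risk depends on a trend existing, on the cost sample and on which method is reported. That is right. National unit costs would also remove price inflation if a single price year were used (not stated), leaving utilisation trend only. Finally, the text does not say outright that the t-test is run on logged costs, and an unadjusted comparison shown descriptively beside a model is ordinary practice.

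**Conclusion.** The t-test is unsuitable for inference in this design: it absorbs about 11 months of calendar trend (10.6 to 11.2 across layouts), treats clustered visits as independent and, on the natural reading, targets geometric means. A utilisation trend could be read as an intervention effect.

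It would be too strong to say that it will be. With log SD 1.0 and no clustering (both assumed), the chance of a spurious finding runs from close to the nominal 5% (1500 patients, 1% a year) to 100% (80,000 visits, 5% a year). It is nearly certain only for the full visit cohort with a trend of about 3% a year or more. Clustering at an assumed ED ICC of 1.9% is enough alone to push the error to about one half at 80,000 visits, but adds little at 1500.

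Nor does this touch a primary conclusion: cost is not among the outcomes listed in Outcomes {12}, and the efficiency remark in the sample-size section is conditional. It is a worthwhile correction to a supporting analysis.

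**What to change.** Remove the t-test as an inferential comparison, or label it descriptive. Name the GLM as the cost analysis and state its essentials: mean cost as the target, with terms for ED-level intervention and calendar period, and allowance for ED and provider clustering, in line with the secular-trend adjustment already promised for DHT/CRM. A gamma model with log link and random effects is one acceptable form; cluster-robust errors with a correction for the small number of EDs is another. Report the difference in marginal mean cost. Apply unit prices from one fixed year, and say which visits enter the analysis.

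The cost is a few lines of wording and slightly more analysis work, with no new data. Intervals will be wider, because part of the information in a simple pre/post contrast is given up to separate the intervention from time.
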